**Objective**

1. To observe the safety and efficacy of a modified Valsalva maneuver (MVM) in VVS patients and find out a new way to treat VVS.

2. To discovery the pathogenesis of VVS and the potential mechanism of MVM on VVS.

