**Methods**

1. Study population

Inclusion criteria: we will recruit VVS patients aged between 18 to 80 years old with at least three lifetime syncopal spells associated with positive head-up tilt testing.

Exclusion criteria: Patients will be excluded if they have other causes of syncope, cannot give informed consent, have serious diseases or psychopath. Women who are pregnant, ready to pregnant, or breast-feeding a baby will be excluded.

2. Divided groups

VVS patients will be randomly divided into two groups: NVM group and MVM group, each 30 patients. Healthy control group (CON group) is 30 patients.

2.1 NVM group: Conventional therapy included: 1) Patient education for the importance of taking enough dietary salt and fluid in daily life. 2) Avoid medications such as diuretics and vasodilators.

2.2 MVM group: conventional treatment plus standard MVM for 50-60 minutes once a day for 30 days.

2.3 CON group: Age and gender matched healthy volunteers without syncope will be enrolled as healthy controls.

3. Study methods

All patients will give informed consent for participation in the study. Age, gender, body mass index, heart rate, blood pressure and biochemical indexes will be record at baseline in the three groups. Frequency and duration of syncope, syncope-induced trauma as well as disease history and current medications will be record in VVS patients.

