**Statistical analysis**

Continuous variables will be presented as mean ± standard deviation (SD). Continuous data with normal distribution will be assessed by Student’s *t*-test or one-way ANOVA with Post Hoc test (Bonferroni) as indicated, and non-normal distribution data will be tested by two-tailed Mann–Whitney U test or Kruskal-Wallis non-parametric test as indicated for the baseline characteristics of the three groups. The Chi-square test will be used to compare the ratio or percentages of categorical variables of the three groups. The Chi-square test will be used to compare the positive rate of HUTT at baseline and after 30 days treatment between NVM and MVM groups. The incidences of recurrent syncopeduring 12 months follow-up of NVM and MVM groups will be compared by log rank test of Kaplan-Meier curve. HRV indexes among the three groups will be assessed by one-way ANOVA with Post Hoc test (Bonferroni) for normal distribution data, Kruskal-Wallis non-parametric test for non-normal distribution data. HRV indexes between baseline and after 30 days treatment will be assessed by Student’s *t*-test for normal distribution data, two-tailed Mann–Whitney U test for non-normal distribution data. The relationship between HUTT and recurrent syncope, HRV and recurrent syncope during 12 months follow-up in VVS patients will be assessed by univariable and multivariable Cox proportional hazards models after 30 days intervention. Receiver operating characteristic (ROC) curves of HRV values at 30 days after intervention will be used to predict 12 months follow-up recurrent syncope. The cutoff values of HRV will be derived from ROC curve analysis by maximizing the sum of the sensitivity and specificity. All statistical analyses will be performed with SPSS version 19.0. *P*<0.05 is considered statistically significant.

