**Expected results**

1 VVS患者存在自主神经功能失调紊乱。

The data will be similar at baseline among the three groups. Positive rate of HUTT will be lower in the MVM group than in the NVM group after 30 days treatment. The incidence of rate of recurrent syncope will be lower in the MVM group than in the NVM group during 12 months follow-up. VVS patients have autonomic nervous function imbalance by HRV analysis among the three groups and between baseline and after 30 days treatment. The underlying mechanism of MVM treating VVS is to improve autonomic nervous function.

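### The HRV analysis names no baseline-adjusted MVM versus NVM comparison: the randomised contrast is at best one of three Bonferroni pairs, and before/after tests cannot carry the mechanism claim

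*Protocol*

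**What the plan says.** The Protocol's Statistical analysis section fixes two analyses of HRV.

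- **Between groups:** "HRV indexes among the three groups will be assessed by one-way ANOVA with Post Hoc test (Bonferroni) for normal distribution data". For non-normal data it names Kruskal-Wallis, with no pairwise follow-up. It does not say whether this is done at baseline, at 30 days or at both.
- **Over time:** "HRV indexes between baseline and after 30 days treatment will be assessed by" Student's t-test, or by a "two-tailed Mann–Whitney U test for non-normal distribution data". The t-test is not described as paired.

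The threshold is P "<0.05 is considered statistically significant". Methods, under Divided groups, gives the sizes: "NVM group and MVM group, each 30 patients", and "Healthy control group (CON group) is 30 patients". The controls are matched healthy volunteers and are not randomised. Holter monitoring is scheduled at baseline and after 30 days in all VVS patients.

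The second objective reads "To discovery the pathogenesis of VVS and the potential mechanism of MVM on VVS". Expected results concludes: "The underlying mechanism of MVM treating VVS is to improve autonomic nervous function". For tilt-test positivity and for recurrence, the Statistical analysis section names NVM versus MVM explicitly. For HRV it does not.

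**The concern.** Two questions share one test. The first is whether VVS patients differ from healthy people. That is a patient-versus-control question, and a comparison that includes the healthy group is reasonable for it. The second is whether MVM changes HRV. Only the randomised comparison of MVM with NVM answers that, and it is most precise when each patient's own baseline HRV is a covariate.

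As written, the second question is served in two weak ways. The post hoc contrast is unadjusted for baseline and shares its error rate with two contrasts against a non-randomised group. The before/after tests make no comparison between arms. The NVM arm also receives advice on salt, fluid and medicines to avoid, and HRV may drift or regress to the mean in either arm, so a change within MVM does not show an effect of MVM. At stake is the mechanistic objective. The clinical outcomes are compared directly between arms and are not affected.

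**Working it through.** **No figure to reproduce.** The protocol gives no HRV effect size, SD, correlation or power.

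**Inputs from the protocol:** 30 per group; significance level 0.05; three groups, hence three pairs and a Bonferroni level of 0.05/3 = 0.0167.

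**Assumed inputs:** two-sided tests; standardised difference d from 0.3 to 1.0; correlation r between baseline and 30-day HRV from 0.3 to 0.7; no loss of patients.

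**1. Power for MVM versus NVM at 30 days.** This applies if the ANOVA is run at 30 days. Noncentral t with noncentrality d / √(1/30 + 1/30). For ANCOVA, replace d by d/√(1 − r²).

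At d = 0.5 the noncentrality is 0.5 / 0.2582 = 1.94. With ANCOVA the effective d is 0.5/√0.91 = 0.524 at r = 0.3, 0.5/√0.75 = 0.577 at r = 0.5, and 0.5/√0.51 = 0.700 at r = 0.7.

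| d | Planned contrast, 0.0167 | Direct two-arm test, 0.05 | ANCOVA r = 0.3 | r = 0.5 | r = 0.7 |
|---|---|---|---|---|---|
| 0.3 | 10% | 21% | 22% | 26% | 36% |
| 0.5 | 31% | 48% | 51% | 59% | 76% |
| 0.8 | 73% | 86% | 89% | 94% | 99% |
| 1.0 | 92% | 97% | 98% | 99% | >99% |

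The planned contrast uses 58 degrees of freedom; the 87 of the three-group ANOVA raise it by no more than about one point. At d = 0.5 the gain has two parts: testing the one randomised contrast at 0.05 takes 31% to 48%, and baseline adjustment takes 48% to 51–76%.

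**2. Difference detectable with 80% power** (normal approximation). (2.394 + 0.842) × √(2/30) = 0.84 SD for the planned contrast. (1.960 + 0.842) × √(2/30) = 0.72 SD for a direct test. Multiplying 0.72 by √(1 − r²) gives 0.63 SD at r = 0.5 and 0.52 SD at r = 0.7.

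**3. VVS patients versus controls at baseline,** d = 0.6 assumed. One arm against controls (30 versus 30) at 0.0167: 45%. All 60 patients against 30 controls at 0.0167: 60%. The same 60 versus 30 at 0.05: 76%. Pooling therefore accounts for 45% to 60%, and using one test instead of three for 60% to 76%.

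**4. Before/after tests when MVM has no effect.** Both arms change by the same amount. If p is the chance that one arm's test is significant, and the arms are independent, MVM alone is significant with probability p(1 − p). The values of p are simulated with 30 per arm and r = 0.7.

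| Change in both arms | p, paired t | MVM alone, paired | p, unpaired t | MVM alone, unpaired |
|---|---|---|---|---|
| 0 | 0.05 | 5% | 0.001 | 0.1% |
| 0.2 SD | 0.28 | 20% | 0.02 | 2% |
| 0.3 SD | 0.54 | 25% | 0.08 | 7% |
| 0.4 SD | 0.78 | 17% | 0.23 | 18% |

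For example, 0.54 × 0.46 = 0.25. Mann–Whitney gives nearly the same as the unpaired t-test. Unpaired tests produce fewer such false patterns at 0.2–0.3 SD only because they waste the pairing: with no change they reject in about 0.1% of arms instead of 5%.

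**The case against.** The strongest reply is that the randomised comparison is not missing. Bonferroni post hoc tests over three groups include MVM versus NVM, and an unadjusted comparison of randomised arms is valid, only less efficient. This stands for normal data: the contrast is diluted and unadjusted, not absent. It does not help in the Kruskal-Wallis branch, where no pairwise step is named.

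A reader might infer that the baseline Holter is thrown away. It is not; the before/after tests use it. What is missing is its use as a covariate in the comparison of arms.

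A reader might also infer that the ANOVA ignores baseline altogether. Its time point is not stated. At baseline it is a legitimate patient-versus-healthy comparison that serves the pathogenesis objective. But if only baseline is meant, no between-arm HRV test exists at 30 days; if 30 days is meant, the contrast is unadjusted. Either way the treatment question is poorly served.

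Expected results states a hypothesis, not a decision rule, and nowhere does the protocol say that significance in one arm and not the other will be read as an effect. That is fair. The protocol does, however, tie its HRV expectations to the three-group and before/after analyses and then states the mechanism, so the risk is real.

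Finally, covariate adjustment is often left to a SAP. Here the protocol positively names the HRV tests, so the point concerns what is fixed, not a detail left open.

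**Conclusion.** The point holds as a recommended change to a secondary, mechanistic analysis. The protocol names no baseline-adjusted MVM versus NVM comparison of HRV, and names no MVM versus NVM contrast at all for non-normal data. The before/after tests cannot fill the gap.

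The size depends on assumed values. At d = 0.5 the planned contrast has 31% power, against 48% for a direct test and 51–76% with baseline adjustment. The planned contrast is the weakest option at every assumed d and r, but low power is not a property of the document: the contrast reaches 73% at d = 0.8 and 92% at d = 1.0.

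The risk that MVM alone appears significant with no treatment effect is about 17–25% with paired tests, for an equal change of 0.2–0.4 SD and r = 0.7, and about 5% with no change. The 17–25% should not be read as describing the tests as written, because the t-test is not specified as paired and Mann–Whitney is an independent-samples test. With unpaired tests the figure is about 2–18%.

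**What to change.** Separate the two questions in the Statistical analysis section.

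1. **Patients versus healthy controls:** at baseline, compare all VVS patients with the control group in one two-group test for each HRV index.
2. **Treatment effect:** compare MVM with NVM by ANCOVA of the 30-day value on arm and the same index at baseline, on the log scale where skewed, in all randomised patients with a 30-day Holter. Report the adjusted difference with a 95% CI.
3. **Mechanism:** base the conclusion on item 2. Present before/after changes and the control group's 30-day values descriptively.

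The cost is mostly wording, since both Holter recordings are already scheduled. One cost goes beyond wording. The accommodation-phase section and the study flowchart exclude MVM patients who do not reach C2 within 10 days, after randomisation and in that arm only. Their scheduled 30-day Holter must be kept for a full randomised comparison; otherwise the limitation should be stated.

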3.2 Twenty-four hour Holter monitoring

Twenty-four hour Holter monitoring will be performed with time domain and frequency domain before HUTT at baseline and after 30 days treatment in all VVS patients.

Time domain parameters

1. standard deviation of NN intervals (SDNN)
2. standard deviation of all 5-min average NN intervals (SDANN)
3. square root of mean of the sum of squares of successive NN interval differences (rMSSD)
4. number of successive NN interval differing by >50ms divided by the total number of successive NN intervals (pNN50)

Frequency domain parameters

1. low frequency (LF): at frequency between 0.04--0.15 Hz
2. high frequency (HF): at frequency between 0.15--0.40 Hz
3. and the low frequency/high frequency ratio (LF/HF)

3.3Detailed procedures of the modified Valsalva manoeuver (MV)

3.3.1 Expiration strength grades and breath-hold time of the modified MV.

Expiration strength is divided into 3 grades (Grade A = 20 mm Hg, Grade B = 30 mm Hg and Grade C = 40 mm Hg). Expiration strength is controlled by blowing into a tube connected to sphygmomanometer. Breath-hold time is divided into 2 lengths (1 = 8 seconds, 2 = 15 seconds).

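### The baseline-to-30-day HRV comparison is within patients, but the protocol assigns it the Mann-Whitney U test, or a t-test not specified as paired

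*Protocol*

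**What the plan says.** Section 3.2 (Twenty-four hour Holter monitoring) schedules the recordings "before HUTT at baseline and after 30 days treatment in all VVS patients". Each patient therefore supplies two values of every HRV index.

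The Statistical analysis section treats HRV in two separate sentences. One compares the three groups by one-way ANOVA or Kruskal-Wallis. The next compares time points: "HRV indexes between baseline and after 30 days treatment will be assessed by Student’s *t*-test" for normal data, and "two-tailed Mann–Whitney U test for non-normal distribution data".

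The same section names the same tests for separate groups at baseline: Student's t-test or ANOVA for normal data, and otherwise "two-tailed Mann–Whitney U test or Kruskal-Wallis non-parametric test as indicated for the baseline characteristics of the three groups". No paired t-test, Wilcoxon signed-rank test or other repeated-measures method is named anywhere in the protocol.

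On size, the Methods section states that "VVS patients will be randomly divided into two groups: NVM group and MVM group, each 30 patients". The significance level is 0.05. Under Expected results, the protocol anticipates that "VVS patients have autonomic nervous function imbalance by HRV analysis among the three groups and between baseline and after 30 days treatment".

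**The concern.** Two measurements on one person are usually correlated. A test that treats them as coming from different people uses the wrong standard error. For non-normal data this is settled by the protocol's own words, because Mann-Whitney U has no paired form. That branch may well be used, since the indexes include a ratio (LF/HF) and a bounded proportion (pNN50). For normal data the form of the t-test is left open.

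The second objective concerns the mechanism of MVM, and the change in HRV over 30 days is one strand of the evidence for it. If that change is tested with the pairing ignored, a real change may come out as non-significant and be read as evidence against the mechanism.

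**Working it through.** The protocol gives no power, SD, expected change or correlation for HRV, so there is no stated figure to reproduce.

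**Inputs from the protocol.** 30 patients per arm (Methods); alpha 0.05; two-sided (stated for Mann-Whitney, taken to apply to the t-test as well).

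**Assumptions.** Within-patient correlation r of 0.5 to 0.8, with 0 and −0.2 as checks; mean change of 0.4, 0.5 or 0.6 SD; bivariate normal values with equal SD; the test run within one arm with 30 complete pairs, and with 60 pairs as a variant.

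**Standard errors, in SD units, for n pairs.**
- Independent form: √(2/n) = √(2/30) = 0.258.
- Paired form: √(2(1 − r)/n) = 0.183 (r = 0.5), 0.141 (r = 0.7), 0.115 (r = 0.8).
- Ratio: 1/√(1 − r) = 1.41, 1.83, 2.24.

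**Type I error.** The independent t-test rejects, on average, when the observed mean change exceeds 2.00 × 0.258 = 0.517 SD (58 degrees of freedom). At r = 0.5 that is 0.517/0.183 = 2.83 true standard errors; at r = 0.7 it is 0.517/0.141 = 3.66. Simulated rejection under no change, at nominal 5%:

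| r | independent t | Mann-Whitney U |
|---|---|---|
| −0.2 | 7.1% | 6.6% |
| 0 | 5.0% | 4.8% |
| 0.5 | 0.7% | 0.7% |
| 0.7 | under 0.1% | under 0.1% |

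**Power, 30 pairs, independent t versus paired t (simulated).**

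| change | r = 0.5 | r = 0.7 | r = 0.8 |
|---|---|---|---|
| 0.4 SD | 27% vs 56% | 23% vs 78% | 19% vs 92% |
| 0.5 SD | 47% vs 75% | 47% vs 93% | 46% vs 99% |
| 0.6 SD | 67% vs 89% | 71% vs 98% | 75% vs over 99% |

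The share of the paired test's power that is lost is 1 − independent/paired. At 0.4 SD and r = 0.5 this is 1 − 0.273/0.559 = 51%. Across r = 0.5 to 0.8 it is 51% to 79% at 0.4 SD, 38% to 54% at 0.5 SD, and 24% to 27% at 0.6 SD. At r = 0 nothing is lost.

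The rank tests behave alike. At 0.5 SD, Mann-Whitney U versus Wilcoxon signed-rank gives 44% vs 74% (r = 0.5), 43% vs 92% (0.7) and 43% vs 98% (0.8).

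**Power, 60 pairs (both arms pooled), 0.5 SD.** 86% vs 97% (r = 0.5), 91% vs over 99% (0.7), 95% vs 100% (0.8). The share lost is roughly 5% to 12%.

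The simulations used 40,000 runs for the t-tests and 10,000 for the rank tests; repeat runs differ by about a percentage point.

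**The case against.** Several points can be made for the protocol.

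- *Student's t-test also covers the paired form.* This stands. A reader might infer the independent form, because the name stands beside Mann-Whitney U and the same pair of tests is used for separate groups. That is inference. For normal data the defect is an unspecified form; only the non-normal branch is wrong on the text itself.
- *The loss of power may be small.* This stands in part. A reader of the 0.4 SD row might conclude that most of the power is lost. The documents do not support that as a general statement, because they give neither correlation nor expected change, and do not say whether the test is run per arm or on all VVS patients. The loss runs from none to very large.
- *Confidence intervals are not affected.* A reader might infer that reported intervals would be too wide. The protocol plans no interval for this comparison, so this would apply only if one were added.
- *The error is on the safe side.* With positive correlation it is: false positives become rarer. With negative correlation it would not be.
- *HRV evidence does not rest on this test alone.* True. The three-group comparison, the Cox models and the ROC curves of 30-day HRV do not depend on it.

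The possibility of a separate SAP does not remove the point. The protocol does not leave the test open for non-normal data; it names one that does not fit.

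**Conclusion.** The concern holds in limited form. For non-normal HRV data the named test is wrong for paired measurements; for normal data the protocol does not say that the t-test is paired. If independent forms are used, the P values are invalid unless the two measurements are uncorrelated, and they are conservative under positive correlation. The size of the damage rests on the assumed correlation, effect size and number of pairs, so the supported statement is that a real HRV change may be missed, not that it will be.

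The consequence is confined to one strand of the mechanism objective. The randomised comparisons of HUTT positivity at 30 days and of syncope recurrence over 12 months do not use this test. The correction should be made before analysis, but the trial's main conclusions do not depend on it.

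**What to change.** Replace the sentence on HRV between baseline and 30 days with one that:

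1. names the paired t-test on within-patient changes, or the Wilcoxon signed-rank test if the changes are not normally distributed;
2. checks normality on the changes, not on the raw values at each time;
3. says whether the test is run within each arm or on all VVS patients, and that it uses patients with both recordings, so that the number of pairs may fall below 30 per arm;
4. calls within-arm results descriptive, with any claim that MVM changes HRV resting on the comparison between the two randomised arms.

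The cost is a short rewrite of one sentence. No extra data are needed, and both tests are standard in the software that the protocol names.

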**The safety and efficacy of modified step-up graded Valsalva manoeuver in patients with vasovagal syncope**

**(Version 1.0 August 20, 2012)**

**Department of Cardiology Puai Hospital**

**Abstract**

Therapeutic options for vasovagal syncope (VVS) remain challenging now. Non-pharmacological therapies, especially the physical maneuvers, are viewed as important and promising strategies for reducing the syncope recurrences. We will plan to recruit 60 VVS patients with syncope history and positive head-up tilt table testing (HUTT). They will be randomly divided into conventional treatment group (NVM group, n=30) and conventional treatment plus standard MVM for 30 days group (MVM group, n=30). The rate of positive HUTT after 30 days treatment and incidence of recurrent syncope during 12 months follow-up will be observed between the two groups. Heart rate variability (HRV) indexes among the three groups and between baseline and after 30 days treatment will be analyzed. The safety and efficacy of the modified Valsalva maneuver (MVM) in VVS patients will be observed. We attempt to find out a new way to treat VVS and discovery the pathogenesis of VVS and the potential mechanism of MVM in VVS.

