3.3.2.2 Accommodation phase

The MV maneuvers will be performed in the morning session consisted 8 VM and in the afternoon session consisted 7 VM. Patients will be asked to perform VM from A1 level to C2 level gradually. Patients who do not reach the C2 level within 10 days will be excluded from the study.

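### The Cox models for 30-day HUTT and HRV pool both randomised arms without naming treatment, so an arm effect could be read as a marker effect

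*Protocol*

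**What the plan says.** The Statistical analysis section of the protocol sets out the marker analysis in one sentence. It takes HUTT and HRV, each against later recurrence, and says that the association "in VVS patients will be assessed by univariable and multivariable Cox proportional hazards models after 30 days intervention". The population is the syncope patients as a whole, that is, the NVM and MVM arms together. The next sentence of the same section uses HRV measured 30 days after intervention, so the markers are taken here to be the post-treatment values. The sentence names treatment neither as a covariate nor as a stratum, and it gives no covariate list for the multivariable model.

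Section 3.2 (Holter monitoring) defines four time-domain indices (SDNN, SDANN, rMSSD, pNN50) and three frequency-domain ones (LF, HF, and their ratio).

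On what treatment is expected to do, Expected results states: "Positive rate of HUTT will be lower in the MVM group than in the NVM group after 30 days treatment". It also expects fewer recurrences in the MVM arm and attributes the benefit to improved autonomic function, which HRV is meant to measure.

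On numbers, Methods states: "VVS patients will be randomly divided into two groups: NVM group and MVM group, each 30 patients". No recurrence rate, HUTT rate at 30 days or event count is given.

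**The concern.** A marker measured at 30 days is a post-randomisation variable. On the protocol's own expectations, the randomised arm moves the marker and also moves recurrence. When the arms are pooled and arm is left out, patients with a negative HUTT are mostly MVM patients and patients with a positive HUTT are mostly NVM patients. The marker then stands in for the arm and inherits the arm's difference in recurrence, whether or not it carries any information among patients treated alike.

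The second objective of the trial is the mechanism by which MVM works. A pooled association between 30-day HUTT or HRV and recurrence is likely to be read as support for that mechanism. The pooled model cannot distinguish a marker that predicts recurrence among patients treated alike from one that merely differs by arm.

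**Working it through.** **Inputs from the protocol.** 30 patients per arm, 60 in total (Abstract; Methods, section 2); 12 months of follow-up after the 30-day therapy (section 3.4); P<0.05, taken as two-sided; candidate markers 1 (HUTT) + 4 (time domain) + 3 (frequency domain) = 8.

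**Inputs assumed.** The proportion HUTT-positive at 30 days and the 12-month recurrence in each arm. The protocol gives neither, so a range is shown. The protocol has no figure of its own to reproduce on this point.

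**Hand check of one case.** Assume HUTT is positive in 80% of NVM and 30% of MVM patients, that recurrence is 50% and 20%, and that HUTT has no effect within either arm.

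- HUTT-positive: 24 NVM and 9 MVM. Expected recurrences 24 × 0.5 + 9 × 0.2 = 13.8 of 33, or 41.8%.
- HUTT-negative: 6 NVM and 21 MVM. Expected recurrences 6 × 0.5 + 21 × 0.2 = 7.2 of 27, or 26.7%.
- Ratio of cumulative hazards: ln(1 − 0.418) / ln(1 − 0.267) = 0.542 / 0.310 ≈ 1.75.

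So a marker with a hazard ratio (HR) of 1 in each arm has a pooled HR of about 1.75.

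**Simulation over a range.** 30 patients per arm, exponential times, censoring at 12 months, Wald test at 0.05, 3,000 runs per row. HUTT depends on arm only and recurrence depends on arm only. HRs are medians.

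| HUTT-positive, NVM / MVM | Recurrence, NVM / MVM | Pooled HR | Pooled P<0.05 | HR with arm | P<0.05 with arm |
|---|---|---|---|---|---|
| 80% / 50% | 40% / 20% | 1.34 | 5.1% | 1.01 | 4.9% |
| 90% / 50% | 50% / 20% | 1.78 | 9.9% | 1.01 | 4.1% |
| 80% / 30% | 50% / 20% | 1.75 | 19.6% | 0.99 | 5.3% |
| 80% / 30% | 60% / 20% | 2.00 | 32.4% | 0.99 | 4.9% |
| 90% / 30% | 60% / 20% | 2.43 | 43.5% | 0.98 | 6.5% |
| 90% / 50% | 50% / 50% | 0.99 | 4.6% | 0.98 | 5.1% |

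The third row matches the hand check. In the first row the HR is biased although the error rate is close to nominal. In the last row MVM does not change recurrence and there is no distortion.

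A separate simulation that stratified by arm (1,500 runs) agrees. With HUTT positive in 80% of NVM and 35% of MVM patients and yearly hazards 0.9 and 0.3, the pooled HR was 1.65 with 19.0% false positives, against 1.00 and 5.9% stratified. With 80% and 50%, and hazards 0.9 and 0.4, it was 1.33 and 7.3% against 1.00 and 4.4%.

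**Number of terms, if most markers were entered together.** Events per term = events / terms. The ceiling, with every patient recurring, is 60 / 8 = 7.5. At an assumed recurrence of 20% to 50% (12 to 30 events) it is 12 / 8 = 1.5 to 30 / 8 = 3.75. The rule in section 3.3.2.2 ("Patients who do not reach the C2 level within 10 days will be excluded from the study") can only lower the 60. With arm, HUTT and one HRV index the figure is 12 / 3 = 4 to 30 / 3 = 10.

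With eight predictors that have no true effect, at least one reached P<0.05 in 37% to 43% of 1,000 simulated trials at each recurrence rate. The apparent c-index ran from 0.73 (12 events) to 0.65 (30 events), where the truth is 0.50. Most of the 37% to 43% is multiplicity: eight independent tests alone give 1 − 0.95^8 = 33.7%.

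**The case against.** Four points can be made in the protocol's defence.

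- **The distortion is conditional.** It needs MVM to affect recurrence at least partly by a route other than the marker. Expected results proposes the opposite, that MVM works through autonomic function. If a marker carries the whole effect, its pooled association is real. This stands, and it means one cannot say that treatment effects will appear as marker effects, only that they could. But the pooled model cannot tell the two situations apart, which is what an analysis of mechanism has to do.
- **A pooled association is legitimate for prognosis.** The section speaks of a relationship and then of prediction, and it plans no formal mediation claim. This stands in part: the pooled figure is a valid description of a mixed population, but a poor guide to the marker's meaning for patients on one given treatment.
- **The sizes rest on assumed rates.** This stands. The false-positive rate runs from nominal to 44% depending on inputs the protocol does not give.
- **The covariate list may be in a statistical analysis plan that is not shown.** This stands for the multivariable model. A reader might infer that this model is overfitted, that it omits treatment, or that LF, HF and their ratio enter together. The protocol says none of these things. The ratio is also a non-linear function of LF and HF, so entering all three would be redundant but not in itself inestimable. The objection does not rescue the univariable models, which have a single predictor and so exclude arm.

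A reader might also infer that the time origin is wrong. Section 3.4 already counts the year of follow-up from the end of the 30-day therapy.

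**Conclusion.** The point holds in a conditional form. As written, the univariable Cox models pool both arms without treatment. If MVM changes both marker and recurrence, and acts at least partly outside the marker, a marker that is null within arms could be declared predictive. Under the assumed rates where MVM lowers recurrence, the pooled HR for such a HUTT marker is about 1.3 to 2.4 with 5% to 44% false positives, against about 1.0 and 4% to 7% with arm in the model. No corresponding figure was computed for HRV, but the reasoning is the same.

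The remark on model size is also conditional. It applies only if most of the eight candidates enter one model, in which case 60 patients could not support it.

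The consequences are confined to the supporting analyses of prognosis and mechanism. The log rank test of recurrence and the chi-square test of HUTT compare the arms directly and do not depend on these models.

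**What to change.** In the Statistical analysis section:

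- State that every Cox model relating 30-day HUTT or HRV to recurrence, including those with a single marker, is stratified by randomised arm or includes arm as a covariate.
- Limit the multivariable model to arm, 30-day HUTT and one HRV index named in advance. Even this has only about 4 to 10 events per term at the assumed recurrence rates, so the estimates need cautious reading.
- Report these results as exploratory associations, not as evidence of mechanism.

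This is a change of wording, with no new data or patients. The cost is that the associations may look weaker and less precise, because differences between the arms no longer contribute to them.
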